### 3.7. Sample size and power calculation

The sample size calculation was based on detecting the changes in primary outcome, the total scores of parental health literacy after 9-month intervention between the intervention and the control group. We assume that the intra-cluster correlation coefficient is 0.05 and that the coefficient of variation is 0.2 according to a previous survey (10). Based on this assumption, 949 participants (73 in each CHC) are needed to detect a difference of 15 in total score between the intervention and the control groups at 0.05 significance level, 90% power. Given an estimated lost follow-up rate of 20%, a total of 1,183 (91 in each CHC) primary caregivers with children aged 0 to 2 years at the recruitment will be needed. All sample size and power calculations were performed using the PASS software (Power Analysis and Sample Size, Version 15, NCSS, Georgia).

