**Methods:**

The cluster randomized controlled trial includes all 13 community health centers (CHCs) in Minhang District, Shanghai. We take each CHCs as a cluster in the randomization. The CHCs are randomly allocated to the intervention or the control group through random sequence generation. Ninety primary caregivers of children aged 0 to 2 years will be recruited from each CHC, 1170 in total. Caregivers in the intervention group will be provided with a series of video clips and online reading material links on scientific parenting *via* a WeChat account. Caregivers in the control group will receive printed educational materials with similar contents to the intervention group. All the participants will access routine child health care and be followed up for 9 months. Online assessment of health literacy will be conducted for both groups before and after the intervention. The primary outcome is the change in the total scores of parental health literacy using a validated instrument. The data of secondary outcomes, such as exclusive breastfeeding in the first 6 months, anthropometric measurements, and disease conditions, will be extracted from routine health care records. Generalized linear mixed model (GLMM) will be used for data analyses.

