### 3.10. Data analysis plan

Descriptive statistic analysis will be performed for all outcomes. For continuous variables, means will be compared using *t*-tests, or non-parametric equivalents for non-normally distributed variables. For categorical variable, chi-squared tests will be used. WHZ, HAZ, WAZ, BAZ, and HCZ will be calculated using WHO Anthro v3.2.2, as the World Health Organization suggested (31).

Generalized linear mixed model (GLMM) will be used for assessing intervention effects on parental health literacy. Covariates will include demographic characteristics and baseline scores. Each CHC will work as a single random effect. This model controlling for the correlation between baseline and follow-up values will not require a random effect for time or a Time × Group interaction term to interpret intervention effects (32). Additionally, given the relatively small number of clusters, the Satterthwaite correction will be used in GLMM to maintain an appropriate Type I error (33). The Satterthwaite correction could achieve an approximation of the degree of freedom according to the residual variances at different levels of each variable (34). The same method will be used for the analyses of secondary outcomes such as parenting behaviors, children's growth, and health outcomes.

All analyses will be conducted with “intention to treat” analysis and multiple imputation will be used to impute the missing entries based on participants' demographics. Results with a Type I error rate of *p* < 0.05 in two-sided tests will be considered statistically significant. All analyses will be performed using SPSS software for Windows (version 22.0; SPSS Inc.) and R Statistical Software (version 4.1.2).

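### The Abstract sets recruitment at 90 per CHC (1,170) but section 3.7 says 91 per CHC (1,183) are needed; the inflation was also rounded down, with negligible effect on power

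*Protocol article*

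**What the plan says.** The Abstract, under Methods, sets the target as follows: "Ninety primary caregivers of children aged 0 to 2 years will be recruited from each CHC, 1170 in total".

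Section 3.7 derives a different one. It starts from the number to be analysed: "949 participants (73 in each CHC) are needed to detect a difference of 15 in total score", "at 0.05 significance level, 90% power". It then allows for attrition: "Given an estimated lost follow-up rate of 20%, a total of 1,183 (91 in each CHC) primary caregivers" are to be enrolled. Section 3.10 makes the tests two-sided.

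Both targets concern caregivers of children aged 0 to 2 years at enrolment in the same 13 CHCs.

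**The concern.** Each target is exact in itself (90 × 13 = 1,170 and 91 × 13 = 1,183). Neither can be put down to a misprinted digit or a round approximation. Section 3.7 describes 1,183 as the number needed, so on the article's own terms the Abstract plans to enrol fewer than that.

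The figure of 949 completers is also not recovered from either target at the loss rate that section 3.7 assumes.

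The planned sample size is a benchmark against which the trial report will be read. Enrolment of 1,175, for example, would exceed the Abstract's target and miss that of section 3.7. A reader who sees only the Abstract carries away a number that the sample size section does not support.

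**Working it through.** **Inputs from the article**
- 13 clusters (section 3.5).
- 949 completers, 73 per CHC; 20% loss; difference of 15 points; significance level 0.05; power 90%; ICC 0.05; coefficient of variation (CV) 0.2 (all section 3.7).
- Two-sided testing (section 3.10).
- Targets of 1,170 (Abstract) and 1,183 (section 3.7).

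**Step 1. Reproduce the figure in section 3.7.** The usual inflation is N/(1 − d).
- Per CHC: 73/0.8 = 91.25. Rounded down, this is 91, and 91 × 13 = 1,183, the stated figure. Rounded up, it is 92, and 92 × 13 = 1,196.
- In total, without equal clusters: 949/0.8 = 1,186.25, rounded up to 1,187.
- The common mistake N × (1 + d) would give 949 × 1.2 = 1,138.8, or 1,139. It was not made.

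The form of the inflation is therefore right. Only the direction of rounding is off.

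**Step 2. Expected completers at 20% loss**

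| Enrolled | Per CHC | Completers | Per CHC | Against 949 |
|---|---|---|---|---|
| 1,170 | 90 | 936.0 | 72.0 | −13.0 (1.4%) |
| 1,183 | 91 | 946.4 | 72.8 | −2.6 (0.3%) |
| 1,187 | unequal | 949.6 | 73.05 | +0.6 |
| 1,196 | 92 | 956.8 | 73.6 | +7.8 |

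The largest loss that still leaves 949 is 1 − 949/1,170 = 18.9% for the Abstract's target and 1 − 949/1,183 = 19.8% for that of section 3.7.

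**Step 3. Effect on power.** Section 3.7 gives no SD, so the 949 cannot itself be reproduced. The cost of a smaller cluster can still be found by taking 90% power at 73 per CHC as given. For m completers per CHC, with equal clusters:
- Design effect: DE = 1 + (m − 1) × 0.05.
- The variance of the difference is proportional to DE/m. The SD and the split of clusters between arms are common factors and cancel in the comparison.
- At m = 73: DE = 4.60 and DE/m = 0.06301.
- At m = 72: DE = 4.55 and DE/m = 0.06319. The ratio is 1.0029, so the standard error rises by a factor of 1.0014.
- At 90% power, difference/SE = 1.960 + 1.282 = 3.242. At m = 72 it is 3.242/1.0014 = 3.237, and power = Φ(3.237 − 1.960) = 89.9%.

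The full calculation was run with 6 against 7 clusters (assumed; the article does not give the split), with CV 0 and with CV 0.2 taken as variation in cluster size (DE = 1 + ((CV² + 1)m − 1) × ICC), and with a normal test and a t-test on 11 degrees of freedom. The SD was solved so that 73 per CHC gives exactly 90%; it came out between about 29.7 and 33.1. Every variant gave 89.92% at 72 per CHC and 89.98% at 72.8 per CHC.

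**The case against.** The strongest reply is that all this is rounding. The right inflation formula was used. The shortfall under section 3.7 is 2.6 people over 13 centers, and no estimate of dropout can tell 19.8% from 20%. A journal abstract is not the document from which centers recruit, and the section that derives the target is unambiguous. A report could simply cite section 3.7, and whether the target was met would be in doubt only if enrolment fell between 1,170 and 1,182.

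Most of this stands, and it rules out three stronger readings.
- **That the trial is underpowered on this account.** A reader might infer this from the missing completers. The article does not support it, since the loss is below 0.1 percentage point.
- **That centers cannot tell when recruitment is complete.** The article does not say what the centers work from, and a fuller protocol may give them one number.
- **That 92 per CHC is the only correct inflation.** It follows only if clusters are held equal. Otherwise 1,187 suffices.

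The reply does not dispose of the contradiction. Leaving detail to a fuller document is normal in an article. Here, though, the article states the same quantity twice, with two values and no explanation.

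**Conclusion.** The contradiction between 1,170 (90 per CHC) and 1,183 (91 per CHC) is certain and should be removed. The rounding point is true but secondary: at 20% loss the two targets leave 936 and about 946 expected completers, not 949.

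The change in power is under about 0.1 percentage point. That rests on taking the stated 90% at 73 per CHC as correct and on an ICC of 0.05. The full run also assumed a 6:7 split, a back-solved SD and CV read as variation in cluster size. If the CV means SD divided by mean, the SD depends on a mean score that the article does not give, and the absolute power at 73 per CHC cannot be checked.

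**What to change.** - State one recruitment target in both the Abstract and section 3.7. The simplest course is to change the Abstract to 91 per CHC, 1,183 in total.
- Beside it, give the expected completers at 20% loss: 946 for 1,183, or 936 if 1,170 is kept.
- Restate power at that cluster size from the sponsor's own PASS inputs. The 89.9% above should not be printed, because it rests on an SD that the article does not give.
- If 949 completers is to remain the stated requirement, set the total to at least 1,187, or to 92 per CHC (1,196) with equal clusters.

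The cost is a correction of text and one rerun of the power calculation. Keeping 1,183, with completers and power restated, adds no one to the number in section 3.7. Going to 1,187 adds 4 caregivers to it, and going to 1,196 adds 13.

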### 3.8. Data collection

The primary outcome of the program is the change in total scores of parental health literacy, which will be assessed by a validated questionnaire, the Chinese Parental Health Literacy Questionnaire of Children 0 to 3 years old (CPHLQ) (10, 11). The CPHLQ was established within the framework of integrated theoretical model of health literacy developed by EU WHO (9) and has been shown with good reliability and validity among primary caregivers of children under 3 years across different regions in China (10, 11, 26). This questionnaire consists of a 39-item subscale for physical health literacy and a 35-item subscale for psychological health literacy, the Cronbach's alpha of which is 0.915 and 0.918, respectively (26). The physical subscale focuses on health literacy toward scientific child feeding, unintended injury prevention, scientific parental care, obesity and undernutrition, Vitamin D and iron deficiency, oral and visual health care, immunization, routine health checkups, antibiotic use, and common childhood diseases “pneumonia and diarrhea.” The psychological subscale focuses on process and milestone of children's early psychological development, problems and treatment of children's psychological development, environment beneficial to children's psychological development, appropriate parenting style, and early learning. Both the physical and psychological part use a percentage grading system, with full score of 100 for each part and a total score of 200.

Secondary outcomes will include: (1) the awareness rate of vitamin D (VD) supplementation after birth; (2) parenting behaviors such as the rate of exclusive breastfeeding (EBF) in the first 4 and 6 months, the rate of breastfeeding in the first 12 and 24 months, and introduction of Iron-fortified staple foods at 6 months; (3) anthropometric measurements of children such as weight-for-length z-score (WHZ), length-for-age z-score (HAZ), weight-for-age z-score (WAZ), BMI-for-age z-score (BAZ), and head circumference-for-age z-scores(HCZ); (4) health outcomes of children such as the incidence of unintended injuries, hospitalization, diarrhea, obesity, and anemia.

Both baseline and final evaluation at the end of nine months survey will be conducted online *via* the aforementioned WOA. Besides collecting data for the outcome measures, we will collect demographic information of the caregiver-child dyads. We will also evaluate participants' engagement of the intervention through their completion rate of video clips and number of times of video watching, which both can be automatically tracked by a functional module designed by the research team on WOA platform.

#### 3.8.1. At baseline

In the baseline survey, demographic information will be collected *via* online questionnaire survey, including caregiver's relationship with the child, education level, source of parental information access, family income, number of children, child's age, gender, and Hukou [the Chinese official residency registration by location, which is directly related to social welfare and administration (27, 28)]. Then an assessment on parental health literacy will be conducted using the CPHLQ. In addition, we will collect parents' self-reported priority needs on parental health literacy, through a multiple-choice question with options involving the topics included in CPHLQ.

#### 3.8.2. At 9 months

After nine-month intervention, online assessment will be conducted again in both intervention and control groups. We will compare the changes of scores on parental health literacy of the two groups to evaluate the efficacy of the WOA-based intervention. We will also collect information on participants' awareness of VD supplementation, parenting behaviors including routine checkup of child's vision and oral health, and children's health outcomes such as occurrence of unintended injury, hospitalization, and diarrhea.

Data on exclusive breastfeeding, breastfeeding, timing of introducing solid foods, anthropometry, and disease conditions such as obesity and anemia, will be extracted from health records from CHCs, which will be collected and recorded by doctors as part of a routine child health checkups (29). Anthropometric measurement will be conducted using established methods and a standard protocol (30).

### 3.9. Data management

Data will be kept anonymous in a server that supports the instant update and confidentiality, and will be used only for this study. Data will be password protected and only authorized research team members will have the access to the links of the database.

### 3.10. Data analysis plan

Descriptive statistic analysis will be performed for all outcomes. For continuous variables, means will be compared using *t*-tests, or non-parametric equivalents for non-normally distributed variables. For categorical variable, chi-squared tests will be used. WHZ, HAZ, WAZ, BAZ, and HCZ will be calculated using WHO Anthro v3.2.2, as the World Health Organization suggested (31).

Generalized linear mixed model (GLMM) will be used for assessing intervention effects on parental health literacy. Covariates will include demographic characteristics and baseline scores. Each CHC will work as a single random effect. This model controlling for the correlation between baseline and follow-up values will not require a random effect for time or a Time × Group interaction term to interpret intervention effects (32). Additionally, given the relatively small number of clusters, the Satterthwaite correction will be used in GLMM to maintain an appropriate Type I error (33). The Satterthwaite correction could achieve an approximation of the degree of freedom according to the residual variances at different levels of each variable (34). The same method will be used for the analyses of secondary outcomes such as parenting behaviors, children's growth, and health outcomes.

All analyses will be conducted with “intention to treat” analysis and multiple imputation will be used to impute the missing entries based on participants' demographics. Results with a Type I error rate of *p* < 0.05 in two-sided tests will be considered statistically significant. All analyses will be performed using SPSS software for Windows (version 22.0; SPSS Inc.) and R Statistical Software (version 4.1.2).

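### The descriptive analysis of outcomes prescribes t-tests and chi-squared tests with no allowance for CHC clustering; for the literacy score a nominal 5% test would have a true type I error of about 36% to 40%

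*Protocol article*

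**What the plan says.** All of the relevant analysis text is in section 3.10 of the protocol article.

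- **Descriptive paragraph.** It begins "Descriptive statistic analysis will be performed for all outcomes. For continuous variables, means will be compared using" t-tests, with non-parametric versions for non-normal data, and continues "For categorical variable, chi-squared tests will be used". It does not mention clusters, the unit of analysis, or a restriction to baseline variables.
- **Effect analysis.** The next paragraph assigns intervention effects on health literacy to a generalized linear mixed model (GLMM). It has demographic and baseline-score covariates, a random effect for CHC and a Satterthwaite correction, which is justified by the small number of clusters. The same method is extended to the secondary outcomes.
- **Significance rule.** The sentence starting "Results with a Type I error rate of" sets a two-sided 0.05 threshold for results in general, not for the GLMM alone.

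Section 3.5 randomises 13 CHCs. Section 3.7 states "We assume that the intra-cluster correlation coefficient is 0.05" and arrives at "949 participants (73 in each CHC) are needed to detect a difference of 15 in total score".

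**The concern.** A description of outcomes needs means, standard deviations and percentages. It does not need hypothesis tests. Ordinary t-tests and chi-squared tests treat every caregiver as independent, yet treatment is assigned to whole CHCs and the sample size calculation itself assumes that caregivers within a CHC are correlated. Ignoring a positive correlation understates the standard error of the difference between arms, so the p-values are too small on average.

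At stake is a set of unadjusted p-values on the outcomes, each open to being called significant at 0.05. Section 3.8 lists many secondary outcomes, so some nominally significant unadjusted differences would be expected even with no effect. It is also inconsistent to protect the type I error in the GLMM with a small-sample correction and then print tests on the same outcomes that have no protection.

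**Working it through.** **Inputs from the documents**
- 13 CHCs (section 3.5). The split is not stated; 7 against 6 is assumed.
- ICC 0.05, stated in the sample size calculation for the literacy total score (section 3.7).
- Caregivers per CHC, m: 73 analysable (section 3.7); 90 recruited (abstract) or 91 (section 3.7). The recruited figure is relevant because section 3.10 plans intention to treat with multiple imputation.
- Two-sided level 0.05 (section 3.10).

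**The plan's own figures**
- 13 × 73 = 949 and 13 × 91 = 1,183, as stated. 73/0.8 = 91.25, which agrees with 91 after rounding.
- The 949 cannot be rebuilt, because no SD is given. With design effect 4.60 and arms of 6 × 73 = 438 and 7 × 73 = 511, the implied SD is 15 / [√(4.60 × (1/438 + 1/511)) × (1.96 + 1.28)] ≈ 33 points. With a t distribution on 11 degrees of freedom it is about 30. The result below does not depend on the SD.

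**True error of an unadjusted test**

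Design effect: DEFF = 1 + (m − 1) × ICC. The unadjusted standard error is too small by √DEFF, so the true type I error is 2 × [1 − Φ(1.96/√DEFF)].

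For the literacy score at ICC 0.05:
- m = 73: DEFF = 1 + 72 × 0.05 = 4.60; 1.96/2.145 = 0.914; error **36.1%**.
- m = 90: DEFF = 1 + 89 × 0.05 = 5.45; 1.96/2.335 = 0.840; error **40.1%**.
- m = 91: DEFF = 5.50; error 40.3%.

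Section 3.7 also gives a coefficient of variation of 0.2 without saying what varies. If it is cluster size, DEFF = 1 + (m × 1.04 − 1) × ICC, and the errors are 36.8% (m = 73) and 40.9% (m = 90).

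**Simulation check** (20,000 trials with no effect, 7 against 6 CHCs, ICC 0.05)
- t-test: 35.8% at m = 73 and 40.2% at m = 90.
- Chi-squared test: 36.5% and 40.2%. These two figures assume a 30% prevalence and carry the literacy-score ICC over to a binary outcome. Neither is in the documents.

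**Secondary outcomes.** No ICC is stated, so these are assumed values:

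| ICC (assumed) | DEFF, m = 73 | Error | DEFF, m = 90 | Error |
|---|---|---|---|---|
| 0.01 | 1.72 | 13.5% | 1.89 | 15.4% |
| 0.02 | 2.44 | 21.0% | 2.78 | 24.0% |
| 0.03 | 3.16 | 27.0% | 3.67 | 30.6% |

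**The case against.** The best defence is that inference on effects is already handled correctly. Section 3.10 gives it to the GLMM for primary and secondary outcomes, and the abstract names only the GLMM. The simple tests sit in an earlier, descriptive paragraph, and no efficacy conclusion is said to rest on them. The wording is also loose: it names neither arms, time points nor unit of analysis, and the reference to all outcomes is in the descriptive sentence while the test sentences speak of variables.

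Much of this stands, and it rules out several stronger readings that a reader might infer:
- **That the trial's conclusions carry a 36% to 40% false-positive rate.** They do not. The rate belongs to the supplementary tests.
- **That the rate holds for every outcome.** The ICC of 0.05 is given only for the literacy score.
- **That each outcome will get two conflicting answers.** The plan says which method assesses effects, and how often the two methods would disagree has not been calculated.
- **That published confidence intervals will be too narrow.** The plan mentions no intervals for these tests.
- **That the plan explicitly prescribes individual-level tests between arms.** This is the natural reading of ordinary named tests under a heading that covers all outcomes, but it is an inference.

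The defence does not remove the point. Nothing confines the tests to baseline, nothing adjusts them for clustering, and the 0.05 rule applies to them as written.

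**Conclusion.** The point holds as a defect in the supplementary tests. If run as written on outcomes between arms, they give invalid p-values: for the literacy score a nominal 5% test has a true type I error of about 36% (73 per CHC) to 40% (90 per CHC). For secondary outcomes the size is unknown; an assumed ICC of 0.01 to 0.03 gives about 14% to 31%.

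This rests on three assumptions: the tests compare individual caregivers between arms; the ICC of 0.05 applies to the literacy measure that is tested; and clusters are of roughly equal size, with a small increase if they are not. The GLMM remains the stated analysis of intervention effects and is untouched by this finding. The correction should be made because it is easy and because invalid p-values would otherwise stand beside valid ones, but it does not threaten the design or the primary analysis.

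**What to change.** Reword the first paragraph of section 3.10 so that outcomes are summarised by arm without p-values, and state that between-arm p-values and intervals for outcomes come only from cluster-adjusted models. If the tests were meant for another purpose, such as describing baseline characteristics, the text should say so and exclude outcomes.

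If an unadjusted comparison is wanted, either of these respects the randomisation:
- the same mixed model with only arm and the CHC random effect, with Satterthwaite degrees of freedom; or
- for continuous outcomes, or for proportions summarised by CHC, a t-test on the 13 CHC means, with 13 − 2 = 11 degrees of freedom.

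The cost is analysis-plan wording. Design, sample size and data collection do not change. The downside is that unadjusted p-values become less favourable than those from the simple tests.
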